### Participant Timeline

The schedule for data collection is outlined in Figure 1. The DARS is independently completed online by participants who volunteer to participate. Questions on the online platform also confirm that they are professional, research, or academic members of the university community, aged >18 years, do not have a diagnosis of schizophrenia or MDD, and are interested in music. If these questions are confirmed and their score is <44 on the DARS, they are contacted by the research team to complete an intake interview, where this information is confirmed along with their English literacy skills, reflective cognitive capacity, and understanding of the requirements of the study. Times are then scheduled at the study center for further preintervention testing, including completion of the SHAPS and fMRI data acquisition. Brief interviews are conducted following the data acquisition to identify any feasibility issues with the music task. Following scans, participants commence 4 months of weekly meetings with the interventionist and undertake the daily music activities. Following completion of the intervention, participants return to the study center to complete the posttest measures of the DARS, SHAPS, and fMRI data acquisition and then participate in an exit interview.

**Figure 1. F1:**

Schedule for data collection. DARS: Dimensional Anhedonia Rating Scale; fMRI: functional magnetic resonance imaging; SHAPS: Snaith-Hamilton Pleasure Scale.

### Sample Size

A sample size of 13 was selected to provide adequate depth of qualitative data (interviews) while maintaining feasibility for resource-intensive fMRI data collection. This sample size is sufficient for exploratory mixed methods analysis and effect size estimation, although it is underpowered for statistical inference [53].

### Imaging Protocol

MRI acquisition will be performed on a 7T Plus research scanner equipped with a 1Tx/32Rx channel head coil (Nova Medical Inc). A high-resolution structural T1-weighted image will be obtained from each participant using a magnetization-prepared 2 rapid acquisition gradient echoes (MP2RAGE [54]) sequence for coregistration with the functional images (parallel reduction factor 4, repetition time 5 s, echo time 2.04 ms, and flip angle 4° and 5°) in a 24 cm field of view, with a 330×330 pixel matrix, in-plane voxel size of 0.75×0.75 mm, a slice thickness of 0.75 mm, and 224 sagittal slices aligned parallel to the midline. To minimize head movement during scanning, foam pads will be inserted on either side of participants’ heads. Respiration and cardiac pulse will be recorded during the session at 50 Hz and 200 Hz, respectively, using a respiratory belt (Siemens) and pulse oximeter (Siemens) to be used for physiological noise correction. We will provide participants with insert earphones (Sensimetrics) to reduce acoustic noise from the MRI scanner as well as to deliver an audible-quality acoustic stimulus.

Functional (T2*-weighted) images will be obtained using a multiband and GRAPPA (generalized autocalibrating partially parallel acquisition)-accelerated gradient echo planar imaging sequence [55] in the steady state (multiband factor 6, parallel acceleration factor 2, repetition time 800 ms, echo time 22.2 ms, and flip angle 45°) in a 20.8 cm field of view with an isotropic 1.6 mm in-plane resolution and a slice thickness of 1.6 mm (no gap), with the phase-encoding direction from anterior to posterior. Eighty-four interleaved slices will be acquired parallel to the anterior-posterior commissure line, covering the whole brain. We will collect data for a resting-state scan and 4 functional sequences, as well as a reverse-phase dataset to be used for distortion correction.

The resting-state scan will be acquired over 5 minutes and 20 seconds. We will instruct participants to keep their eyes closed but not to fall asleep for the duration of the scan.

### Functional Imaging Paradigms

#### Reward-Reversal Task

This task is a previously described reversal learning paradigm [56] that aims to characterize reward prediction errors. In brief, we will present participants with a pair of target neutral stimuli (shapes) at the top and bottom of the screen. In each trial, 2 conditions can occur: either the top stimulus will be highlighted, or the bottom stimulus will be highlighted. Participants must predict whether the highlighted stimulus is associated with a reward or a punishment. If participants guess correctly, we will provide feedback with a green thumbs-up in the center of the screen, a pleasant, high-pitched tone, and a notification that they were correct. If they guess incorrectly, we will provide feedback with a red thumbs-down in the center of the screen, a low-pitched tone, and a notification that they were incorrect. Once a participant has reached a pseudorandom learning criterion of between 3 and 6 correct trials in a row, the reward-punishment association of the stimuli will be reversed. After each reversal, the learning criterion will be reset to a pseudorandom number between 3 and 6. The reversal will occur after each subsequent learning criterion is reached for the duration of the task. The total duration of this task is 13 minutes.

#### Music Task

Prior to scanning, participants self-select 5 pleasure-inducing tracks and nominate their most pleasurable 30-second excerpt of each track. Participants then identify 5 tracks with similar musical characteristics that they feel neutral listening to, using the following generative AI prompt:

What are five music recommendations with the same genre, instrumentation, singer gender, range, rhythmic energy, dynamic range as <insert pleasure-inducing track name here>?

This prescan process generates 10×30 seconds music excerpts (5×pleasure-inducing excerpts and 5×neutral excerpts). The music itself was not generated by AI but only identified using the AI prompt.

Within the music task, participants listen to each of the generated music excerpts twice, for a total of 20 × 30 seconds music excerpts (a similar time duration to foundational music chills research [57]), with a 15-second white noise break between each excerpt, running for 15 minutes in total. Participants are directed to close their eyes throughout the task and pay attention to any feelings that arise as they listen. The presentation of excerpts alternates between pleasure-inducing and neutral excerpts (or the reverse), and the order of excerpts is randomized within this alternating framework. All 5 excerpts of each type (pleasure-inducing or neutral) are played once before the sequence repeats a second time in the same order. Participants are manually allocated to start with the neutral or pleasure-inducing excerpts for this task, with the allocation evenly distributed across study participants.

#### Positive and Neutral Naturalistic Music Tasks

Participants will undergo 2 fMRI tasks with continuous music listening. They will preselect 1 of the 5 pleasure-inducing tracks and will listen to it in its entirety on loop for 5 minutes. They will then perform the same fMRI scan but with a corresponding neutral song played in its entirety on loop for 5 minutes.

### Data Analysis

Repeated-measures *t* tests will be conducted on pre-post DARS and SHAPS scores to examine directional change. Hedges *g* will be calculated to estimate effect sizes, which will inform power calculations for a future fully powered study. *P* values will be reported descriptively but not interpreted as indicators of statistical significance, given the small sample size (N=13).

fMRI data will be analyzed using individual general linear models to identify longitudinal changes associated with the intervention. For each task, blocked-design general linear model analyses will be specified at an individual participant level in Statistical Parametric Mapping version 12 (SPM12) to model specific conditions of interest. For the reward-reversal task, this will involve contrasting unexpected punishment trials with expected reward trials. For the music task, the primary contrast will compare pleasurable music with neutral music. Repeated-measures, flexible factorial designs (within-subject factors: primary contrast×time) will be used at the group level to examine longitudinal changes. These will then inform exploratory investigations of associations between these effects and symptom improvement.

Inductive thematic analysis will be used to identify patterns in descriptions of change and group similar ideas from across the interview data [58]. Labels will be selected that verifiably represent the participant quotes contained within each theme, and these will be checked by the research team as a form of peer debriefing to identify blind spots and adjusted when found to be dissimilar.

Sequential analysis will be conducted by comparing the themes from interviews to overall changes in participant scores on psychometric measures of anhedonia from preintervention to postintervention assessments to identify any correspondences. Themes will also be compared to any changes in activity across reward processing regions during reward fMRI tasks and targeted music listening evident from preintervention to postintervention assessments that correspond with patterns of congruence in the psychometric data.

Feasibility will be documented based on verbal feedback following fMRI data acquisition and in the final interview. Anything beyond individual preferences will be used to inform necessary changes to the protocol.

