### Study Design

Given the findings from previous case studies, a sequential mixed methods study design is suitable for use in this pre-post pilot study to explore congruences between psychometric, interview, and fMRI data regarding changes in hedonic capacity among individuals with anhedonia following the music therapy intervention. Neither a strictly explanatory nor exploratory model (according to Creswell and Plano [44] definitions) is used, but the design will prioritize quantitative data from psychometric scales and seek to understand any significant differences from before to after intervention using interview data collected after intervention. This will cautiously extend case study findings of the same music therapy intervention [21,22] to determine whether psychometric outcomes are significant at the group level, as well as to explore patterns in the interview data to better understand any changes on the 2 different outcome measures—the DARS [45] and the Snaith-Hamilton Pleasure Scale (SHAPS) [46]. It would be premature to include a control condition at this stage, and similarly, the sampling of participants will be restricted to high-functioning people with anhedonia to better understand the phenomenon before extending the research to more clinical populations, such as those with schizophrenia or MDD. In addition, the study will assess the feasibility of the intervention and study procedure to inform a subsequent larger-scale study [47]. Feasibility measures will evaluate the acceptability, adherence, and practicality of delivering the intervention in adults with high cognitive function, while preliminary estimates of intervention effects and variability will be used to inform sample size calculations and the design of a future fully powered study.

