### Eligibility Criteria

To identify participants with anhedonia, communications included a link to an online screening survey that prospective participants could independently access, comprising the DARS and questions assessing the inclusion criteria. The research team reviewed all survey responses, and eligible prospective participants were identified as scoring <44 on the DARS [45], based on the group differences identified between patients with major depressive episodes and healthy controls. This score has also been used in a study of university students where none of the healthy controls scored <44 points on the total scale [52]. All participants were required to complete a magnetic resonance imaging (MRI) safety implant checklist and be screened by qualified radiographers to deem them compatible with an MRI scan.

The inclusion criteria are being a professional, research, or academic member of the university community, having the cognitive capacity to select and discuss pleasure-inducing music, being aged >18 years, scoring <44 on DARS, agreeing to participate and having the capacity to provide informed consent, having a self-identified interest in music, and having English literacy skills suitable for participation in interviews. Exclusion criteria for all groups are failure to meet scanning requirements, including having metallic objects in the body (eg, a cardiac pacemaker or cochlear implant), a history of claustrophobia, permanent metal dental appliances, or a body weight ≥120 kg, or having a diagnosis of schizophrenia or MDD.

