### Limitations

The lack of a control group and the small sample size are limitations of the study design. A control group will be included in subsequent studies, once we have determined whether the intervention increases hedonic capacity among individuals with anhedonia and whether any congruences across psychometric results and interview data are identified. This pilot will also enable us to test whether the musical pleasure fMRI paradigm can produce results indicative of reward pathways in those with anhedonia. Nevertheless, it will remain challenging to blind both participants and researchers. The enhanced sensitivity and specificity of fMRI data acquired on the 7T MAGNETOM Plus MRI system may help mitigate the limitations associated with the small number of participants.

There will be some flexibility in the delivery of the intervention since therapeutic integrity is challenged by an overly fixed intervention manual that does not respond to presenting needs. We have published the music therapy intervention [22] that addresses validity and replicability by transparently outlining four categories of principles: (1) unique and essential, (2) essential but not unique, (3) acceptable but not necessary, and (4) not acceptable (proscribed), as recommended in previous music therapy studies [59]. This framework has been used in this study and in additional case studies.

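### Thirteen participants are called enough to estimate an effect size, and the uncontrolled pre-post Hedges g is to inform the power of a controlled trial; it is too imprecise and measures a different effect

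*Protocol article*

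**What the plan says.** The Sample Size section bases the number on interview depth and imaging resources: "A sample size of 13 was selected to provide adequate depth of qualitative data (interviews) while maintaining feasibility for resource-intensive fMRI data collection". It then adds a statistical claim: "This sample size is sufficient for exploratory mixed methods analysis and effect size estimation, although it is underpowered for statistical inference".

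Two places give the effect estimate a role in planning the next study. Data Analysis says of Hedges g on pre-post DARS and SHAPS that it is a quantity "which will inform power calculations for a future fully powered study". Study Design says that "preliminary estimates of intervention effects and variability will be used to inform sample size calculations and the design of a future fully powered study".

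The present study has one arm. Study Design states: "It would be premature to include a control condition at this stage". The Limitations section states: "A control group will be included in subsequent studies".

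Under Eligibility Criteria, "eligible prospective participants were identified as scoring <44 on the DARS". The Outcomes section makes clear that this same screening score is the DARS baseline, while SHAPS is taken on scanning days and plays no part in selection.

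**The concern.** Two things look wrong.

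First, the adequacy claim. The standard error that makes 13 pairs underpowered for inference also sets the precision of g. A sample cannot be too small for the one and sufficient, without qualification, for the other.

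Second, the planned use. A controlled trial is powered on the difference between arms. The pilot g is a change within one arm, so it also contains whatever would have happened without the intervention. More participants would narrow its interval but would not remove that component.

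At stake is the size of the next trial. If a one-arm g is taken over as the target effect, that trial may be several times too small or, if the pilot happens to give a low value, needlessly large or not run at all.

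**Working it through.** **Inputs from the document:** n = 13, one arm, paired pre-post scores, Hedges g; DARS entry score below 44, reused as baseline; the next study controlled.

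**Assumptions, because the document gives no figures:** observed g of 0.3 to 1.0; g standardised by the SD of change; for the next trial, two equal arms, two-sided 5% and 80% power, with its effect expressed on the same SD scale as g. The figure of 13 has no statistical derivation, so there is nothing to reproduce. What can be checked is the precision it gives.

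**Step 1: precision of g.** The small-sample correction is J = 1 − 3/(4 × 12 − 1) = 0.936. For each g, take d = g/J and t = d√13, find the two noncentrality parameters that place t at the 2.5% and 97.5% points with 12 df, divide by √13 and multiply by J. For g = 0.8: d = 0.855, t = 3.08, noncentrality 0.73 to 5.34, interval 0.19 to 1.39.

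| Observed g | 95% CI | Half-width |
|---|---|---|
| 0.3 | −0.23 to 0.82 | 0.52 |
| 0.5 | −0.05 to 1.04 | 0.55 |
| 0.8 | 0.19 to 1.39 | 0.60 |
| 1.0 | 0.34 to 1.63 | 0.64 |

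As a cross-check, the half-width for the mean change in SD units is 2.179/√13 = 0.60. The Hedges correction removes small-sample bias; it does nothing for this width.

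**Step 2: what the interval implies for a two-arm trial.** The number per arm is roughly 2(1.96 + 0.84)²/d² = 15.7/d², plus one or two when the t distribution is used.
- g = 0.8: 26 per arm at the estimate, about 440 at the lower limit (15.7/0.189²), 10 at the upper limit.
- g = 0.5: 64 at the estimate, 16 at the upper limit. The lower limit is below zero, so no finite size exists there.

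**Step 3: one-arm change against between-arm difference.** Suppose g = 0.8 leads to 26 per arm, and untreated people improve by c SD (assumed).

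| c | Net effect | True power at 26 per arm | Needed per arm for 80% |
|---|---|---|---|
| 0.2 | 0.6 | 56% | 45 |
| 0.3 | 0.5 | 42% | 64 |
| 0.4 | 0.4 | 29% | 100 |

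**Step 4: could untreated change be that large on DARS?** Assume normal scores, a cutoff 1.5 SD below the mean of those screened, and retest correlation r. Those selected lie on average λ = φ(1.5)/Φ(−1.5) = 1.94 SD below the mean, with baseline variance 0.150 of the unselected variance. Expected change with no treatment effect is (1 − r)λ; the SD of change is √[(1 − r²) + (1 − r)² × 0.150].
- r = 0.9: 0.19/0.438 = 0.44 SD of change.
- r = 0.7: 0.58/0.724 = 0.80 SD of change.

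With the cutoff 1 SD below the mean, the same range of r gives 0.35 to 0.63. Regression to the mean alone can therefore produce a DARS g of the size one would plan on. In a controlled trial with the same entry rule it would be expected in both arms and would largely cancel. This argument does not carry over to SHAPS in the same form, because SHAPS was not the selection score.

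**The case against.** The strongest reply is that this is an openly modest pilot. Its primary aim is feasibility, P values are descriptive, the sample is declared underpowered, and the small number and lack of controls are listed as limitations. The text says that g will inform power calculations, not that it will be their target or only input. The adequacy statement concerns exploratory work and rests on a cited source that cannot be seen here. Interval reporting and the choice of standardiser are details an article may leave to a fuller plan.

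Much of this stands. It shows that no result of the present study is at risk, and that any harm needs a later team to use g uncritically. It does not rescue the two statements themselves. The limitations are never applied to this use of g, and the article offers no other basis for the next trial's effect.

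Three stronger readings are tempting but unsupported:
- **That g will be the sole basis, so the next trial will be undersized.** The documents do not say this; undersizing is a risk that depends on how g is used.
- **That standardising by the SD of change by itself halves the next trial's power.** With an assumed pre-post correlation of 0.8, a raw-SD effect of 0.40 becomes 0.40 × 1.58 = 0.63 and suggests 41 per arm. Power at 41 per arm is 43% only if the trial compares post-test scores and ignores baseline. It is 81% with change scores and 85% with baseline-adjusted analysis. No document fixes that analysis, and at correlation 0.5 the two scales coincide.
- **That the post-test SD escapes the entry restriction.** It does not. Under the Step 4 assumptions with r = 0.8, the DARS post-test SD is about 0.68 of the unselected SD, and the within-sample correlation falls to about 0.46.

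**Conclusion.** The point holds for the adequacy claim and for the planned use of g, and it should be fixed. Thirteen pairs locate g only to within about half an SD or a little more either way, which is too wide to choose between a trial of about 10 and one of about 440 per arm at g = 0.8. That result depends only on n, the 95% level and the assumed g, with standardisation by the SD of change. The mismatch between a one-arm change and a between-arm effect follows from the document's own account of the two designs. Its size, true power of about 56% to 29%, rests on an assumed untreated improvement of 0.2 to 0.4 SD.

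A reader might infer that 13 is the wrong sample size. The documents do not support that: the number is justified by qualitative depth and imaging resources, and nothing here bears on its adequacy for those aims or for feasibility. Nor does the point affect this study's own conclusions, which is why it stops short of a mandatory change.

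**What to change.** **Sample Size:** replace the statement that 13 suffices for effect size estimation with one that effect sizes will be imprecise, with a 95% confidence interval half-width of about 0.5 to 0.65 SD depending on the observed value. Do not give a single half-width, since it grows with g.

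**Study Design and Data Analysis:** state that
- g will be reported descriptively, with its 95% confidence interval and a named standardiser;
- the uncontrolled pre-post g will not be the target effect of the controlled trial, which will be powered on a justified between-group difference;
- the pilot will contribute feasibility rates and, with their uncertainty, the SD and pre-post correlation. For scale, 95% limits for an SD on 12 df run from 0.72 to 1.65 times the observed value. For DARS, note that the SDs and the correlation are affected by selection on a score below 44.

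The cost is wording in three sections and a little extra reporting. Recruitment is complete and no new data are needed. The downside is that the stated value of the pilot for planning becomes more modest, and that a between-group difference must be justified from elsewhere, since the article gives none for either scale.

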### Objectives

Our primary aim is to examine the feasibility of leveraging a music therapy intervention to increase hedonic capacity among individuals with anhedonia. We also aim to examine congruence across psychometric results and interview data to generate estimates of effect size and qualitative experience. In addition, we aim to identify any correspondence between these outcomes and changes in brain activity associated with reward processing during targeted fMRI tasks. This study will generate hypotheses for testing in future studies by investigating the following research questions (RQs):

RQ 1: To what extent is the music therapy intervention feasible, based on measures of participant adherence, engagement, and retention?RQ 2: Do overall changes in participant scores on psychometric measures of anhedonia from before to after the music therapy intervention correspond with patterns in descriptions of change in interviews?RQ 3: Are pre-post changes in activity across reward processing regions during fMRI tasks associated with changes in anhedonia symptoms?

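### If fitted as a 2×2 with one residual, the group-level fMRI model tests contrast×time against an error that is right only under equal stratum variances; a per-participant post-minus-pre contrast avoids this cheaply

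*Protocol article*

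**What the plan says.** The Data Analysis section sets out three steps for the task fMRI data.

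1. First-level general linear models are "specified at an individual participant level in Statistical Parametric Mapping version 12 (SPM12"). For the music task, "the primary contrast will compare pleasurable music with neutral music". For the reward-reversal task, the contrast is unexpected punishment against expected reward.
2. For the second level, "Repeated-measures, flexible factorial designs (within-subject factors: primary contrast×time) will be used at the group level", with longitudinal change as the stated purpose.
3. The results of step 2 then inform exploratory work on how these effects relate to symptom improvement.

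The third research question (Objectives) asks: "Are pre-post changes in activity across reward processing regions during fMRI tasks associated with changes in anhedonia symptoms". Sample Size gives 13 participants and describes this as sufficient for exploratory analysis and effect size estimation, "although it is underpowered for statistical inference".

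The article does not say which images enter the group model, which effect will be read, how many residual df the model has, or how non-sphericity is handled.

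**The concern.** Calling the primary contrast a within-subject factor implies that it has at least two levels, and each task supplies exactly two. With two sessions, that means four images per participant. A single linear model with subject and cell terms has one residual, and every effect is tested against it.

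The right yardstick for contrast×time is how much participants differ in their change in the contrast. The single residual also contains two other sources of variation: stable differences between people in the contrast, and whole-session shifts specific to a person. Both cancel in a difference of differences. Both are plausible here, because the music is self-selected and the scans are about four months apart.

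The article wants the fMRI data to give effect size estimates and to identify regions for later studies (Study Design). A mis-scaled error would alter the test maps from which regions are picked, in a sample that has little sensitivity to spare.

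**Working it through.** The plan gives no alpha, variance, df or power for this model, so there is no figure of its own to reproduce.

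**Inputs.** From the article: n = 13, two conditions per task, two sessions. Assumed: two-sided 5%, residual variance 1, a true standardised change (mean over SD of the difference of differences) of 0.8, and no non-sphericity correction.

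**Degrees of freedom.** There are 13 × 4 = 52 images. Subject plus four cells has rank 13 + 3 = 16, so the residual has 52 − 16 = 36 df. These are three strata of 12 df each. A test of contrast×time on its own stratum has 12 df.

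**Stratum variances.** Let v_SC and v_ST be the subject×contrast and subject×time variances. In orthonormal form the strata are:

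- subject×contrast: 1 + 2·v_SC
- subject×time: 1 + 2·v_ST
- subject×contrast×time: 1

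The pooled error has expectation equal to the mean of the three. With v_SC = v_ST = 0.5 the strata are 2:2:1, with mean 5/3 = 1.667.

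**Approximate check, 2:2:1.** The 36-df critical value is 2.028. For the interaction, measured on its correct standard error, the threshold becomes 2.028 × √1.667 = 2.618. The noncentrality is 0.8 × √13 = 2.884, so power is about Φ(2.884 − 2.618) = Φ(0.266) ≈ 0.605. For time, the threshold becomes 2.028 × √(1.667/2) = 1.851, which has a normal two-sided tail of about 6.4%.

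**Simulation** (true size at nominal 5%; power at a standardised change of 0.8):

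| v_SC, v_ST | Strata | Contrast×time size | Contrast×time power, pooled | Time size |
|---|---|---|---|---|
| 0, 0 | 1:1:1 | 5% | 80% | 5% |
| 0.5, 0.5 | 2:2:1 | 1.2–1.3% | 61% | 7% |
| 1, 1 | 3:3:1 | 0.4% | 43% | 8% |
| 0, 1 | 1:3:1 | 1.4% | 61% | 14% |
| 1, 0 | 3:1:1 | 1.4% | 61% | 1.4% |

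The paired test has 5% size and 75% power in every row. Its critical value is 2.179 on 12 df. In the first row pooling gains 80 − 75 = 5 points. In the second it loses 75 − 61 = 14.

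**The other reading.** If one contrast image per session is entered, with subject and time as the only terms, there are 26 images and 26 − 14 = 12 residual df. On a simulated data set this model and the paired t test gave the same statistic (0.0467), so no error-term problem arises. The 2×2 pooled model on the same data gave 0.0360.

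**The case against.** The strongest reply is that the article nowhere states a pooled error term. It names a design and two factors. Input images, residual df and non-sphericity handling are settings that an article may leave to the full plan. That stands: the defect is conditional on how the model is fitted, and the figures above apply no correction.

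Three stronger readings are tempting, and the documents do not support them.

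- A reader might infer that the flawed test is the answer to the third research question. It is not. That question asks about association with symptom change, and the factorial model only feeds that later step. In a balanced design the error term changes neither the mean interaction nor any participant's post-minus-pre contrast. It changes the standard error and the test, and through them, at most, which regions are carried forward.
- A reader might infer that longitudinal effects will be over-called. For contrast×time, the variance components considered here make the test conservative. Over-calling it would need the opposite ordering of strata: 1:1:2 gives about 11%. Adding subject×contrast or subject×time variance cannot produce that ordering. Over-calling concerns a time main effect, which the article never says it will interpret, and even there it depends on the variances (1.4% when only subject×contrast variance is present).
- A reader might infer that both readings of the sentence have the same fault. With one contrast image per session only the label is loose, because a factor with one level is not a factor.

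It also stands that this is a hypothesis-generating pilot, openly described as underpowered.

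**Conclusion.** The point holds as an improvement to a stated model. It has not been shown that the planned analysis is wrong. On the 2×2 reading with a single uncorrected residual, the interaction test is correctly sized only under equal stratum variances. Under the assumed variances in the table it falls to between 0.4% and 1.4% and loses 14 to 32 power points against the paired test. A time main effect, if one were read, would run at about 7% to 14% where subject×time variance is present.

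These figures rest on variances, an effect size and a 5% level that the documents do not supply. They describe a single test, not a thresholded brain map. No conclusion of the pilot turns on this choice. It matters for which regions are taken into a later study.

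**What to change.** Replace the group-level sentence with a specification along these lines:

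- For each participant and task, compute the first-level contrast at each session (pleasurable minus neutral; unexpected punishment minus expected reward).
- Take post minus pre within each participant and test the mean of that difference image with a one-sample t test on 12 df.
- Regress the same difference image on the symptom change score for the exploratory association in the third research question.
- Do not interpret time main effects from a model with a pooled error.

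If the intention was already to enter one contrast image per session, say so and drop the contrast as a factor.

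The cost is re-specifying the second-level model. The article describes the analysis as still to come, so nothing need be redone. The price is 12 residual df instead of 36, or about 5 power points (75% against 80%) in the case most favourable to pooling. In return, the test keeps its nominal size under every variance pattern tried, and it yields the participant-level change image that the association step needs.
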